### Potential risks for bias

Some potential risks for bias might be expected. First, although patient selection bias should be minimal, it is still possible that it is difficult for nurses to include patients that are unmotivated to change their lifestyles in a lifestyle intervention study. Motivated patients are expected to be more easily included, leading towards patient selection bias based on the level of motivation. Second, because patients determine which lifestyle behaviours they wish to change, it is possible that they target other somatic health outcomes (e.g. dental health, sleeping patterns) than the primary study outcome waist circumferences and other cardiometabolic risk factors. In this case, stating that the intervention does not seem effective in reducing the primary outcome might be a biased conclusion when patients wished to change other health outcomes and might have been successful in addressing these changes. Third, although ROM is implemented on all sites, it is possible that not all sites have the capacity to conduct all measures, leading to missing values. In addition, ROM nurses cannot collect blood samples themselves but send patients an invitation to visit a (hospital) laboratory. Although ROM nurses convince and remind patients to do so, patients might be reluctant to go to the laboratory, also leading to possible missing values.

### Changes in study design between obtaining funding and preparation of the study

In the period between obtaining funding and preparing the study, unexpected large changes in the organisation of mental health care took place. Budgets were restrained and care delivery shifted from specialists towards general mental health care, leading to necessary adjustments in study design. The initial sample size was estimated based on 64 nurses all including 10 patients leading to a target sample of 640 patients. The Medical Ethics Committee advised us to plan an extra 20% inclusion to account for clustering of the data, yielding a target sample of 768 patients. However, due to increased workload, inclusion of twelve patients per nurse seemed unfeasible. To compensate, we planned to train more nurses so that less patients per nurse need to be included, and we furthermore broadened inclusion criteria so that patients in sheltered living facilities could be included as well. As we now had many clusters (teams and nurses) and relatively few patients per nurse, it was not necessary anymore to account for clustering of the data in calculating the sample size. The funding agency (ZonMw) and the Medical Ethics Committee have approved the adjusted study design and adjusted final target sample size of 275 patients.

The somatic health of patients in mental health care can no longer be ignored. Changing lifestyle behaviours is difficult, but combining several successful components (e.g. motivational interviewing, stage-of-change, objective monitoring, self-management, support of peers and family etc.) into one multidimensional intervention might enhance successful, sustainable lifestyle changes.

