### Study setting

Mental health care for severe mentally ill (SMI) outpatients is organized by a Flexible Assertive Community Treatment (FACT) team with MH nurses. FACT means that patient care is outreaching, takes place in the community (patients’ own environment) and ranges from high intensive (24 h) treatment to low intension support – for a detailed description of FACT, see [30, 31]. Patients living in sheltered facilities receive a combination of housing and services in the community. 21 FACT and eight sheltered facility teams serving SMI patients of five mental health care organizations in the North of the Netherlands, an area covering 2.8 million inhabitants, are invited for this study. Per team, nurses are invited to participate. All teams per organization are matched based on caseload size, mean age of patients, mean duration of admission of patients, most frequent diagnosis and location (urban or rural). After matching, teams are randomly allocated to the control or intervention arm by means of a random number generator by a researcher of the research team not involved in training of staff and recruitment of patients (see Fig. 1 for flowchart of the study). To minimise spill-over, randomisation is on team level, although inclusion of study participants and statistical inference are on patient level.

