### Participants

The study population consists of community-dwelling SMI patients and SMI patients living in sheltered facilities. Of this population, approximately 75% of the patients is diagnosed with a psychotic disorder, 15% with bipolar disorder and approximately 10% with complex personality disorders. In the North of the Netherlands, SMI patients are invited for annual Routine Outcome Monitoring screenings as part of standard care, consisting of a physical examination, a lab test and psychosocial measures. Patients are invited for the LION study when ROM screening outcomes indicate at least one of the following risk factors for metabolic syndrome: waist circumference > 88/102 cm (females/males); fasting glucose > 5.6 mmol/L or HbA1c > 5.7%; BMI > 25 kg/m^2^. Exclusion criteria are being pregnant, a BMI < 19 kg/m^2^, being primarily diagnosed with Korsakov syndrome or having a physical impairment which makes daily physical activity impossible. When patients are eligible for the study, they receive a detailed information letter from their case manager and, if willing to participate, sign informed consent.

The main objective of this trial is to detect an abdominal weight loss having public health significance. Previous work has indicated that 5-10 cm reduction in waist circumference (WC) is considered a realistic guideline with a high probability of health benefits [32]. For power calculations, we assumed 10% dropout rate. To include 250 participants, a 10% extra will be needed resulting in a total of 275 patients. Under these assumptions, and assuming an SD of 16.3 cm based on pilot data from this population, for two-sided 0.05-level tests of the null hypothesis, the study should provide approximately 80% power for detecting a difference of 5.8 cm in WC at 12 months between intervention and control groups. In addition, the study will have the same power to detect a reduction of 0.6 mmol/L in plasma glucose, given an SD of 1.7 mmol/L.

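### The stated 80% power for waist and glucose is an individually randomised figure; the reason given for omitting a clustering allowance does not hold when teams are randomised

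*Protocol article*

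**What the plan says.** All places are in the protocol article.

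- **Unit of randomisation** (Methods, Study setting): "To minimise spill-over, randomisation is on team level". The invited teams are 21 FACT teams and eight sheltered-facility teams, 29 in all. They are matched within organisation before allocation. Inference is at patient level.
- **Primary model** (Methods, Statistical analysis): change in waist circumference from baseline, analysed by multilevel linear mixed models with team as the cluster.
- **Power** (Methods, Participants): the waist SD is taken from pilot work as 16.3 cm, and testing is two-sided at the 5% level. The claim made on that basis is that "the study should provide approximately 80% power for detecting a difference of 5.8 cm in WC at 12 months between intervention and control groups". For glucose, where the SD is 1.7 mmol/L, the article says that "the study will have the same power to detect a reduction of 0.6 mmol/L in plasma glucose". Both claims rest on 250 participants after 10% dropout from 275. The section gives no ICC, design effect or team size.
- **Clustering** (Discussion, Changes in study design between obtaining funding and preparation of the study): for the superseded design of 64 nurses with 10 patients each, the Medical Ethics Committee "advised us to plan an extra 20% inclusion to account for clustering of the data", which raised 640 to 768. For the current design the authors plan more nurses with fewer patients each, add sheltered-living patients, and conclude that "it was not necessary anymore to account for clustering of the data in calculating the sample size". The funder and the Committee approved 275.

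**The concern.** The article does not simply leave a design effect to a fuller document. It states that none is needed and gives a reason, and the reason concerns the wrong unit. Nurses work within teams, and teams are what is randomised. Training more nurses in a team lowers the number of patients per nurse but leaves the number per team unchanged. A larger number of clusters helps precision, but it does not make the design effect equal to 1.

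What is at stake is how the result is read. If the trial finds no difference, readers will judge that against 80% power for 5.8 cm, a figure calculated for a different design. A published rationale that clustering can be ignored when patients per nurse are few may also be copied elsewhere.

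**Working it through.** **Inputs from the article.** Two-sided alpha 0.05; waist difference 5.8 cm, SD 16.3 cm; glucose difference 0.6 mmol/L, SD 1.7 mmol/L; 250 analysed; 21 + 8 = 29 teams.

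**Assumptions, because the article gives no figure.** 1:1 allocation, all 29 invited teams taking part, equal team sizes, and an ICC between 0.01 and 0.05.

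**Step 1: reproduce the stated power with no clustering.**

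n per arm = 2 × (1.96 + 0.8416)² × SD² / d²

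- Waist: 2 × 7.849 × (16.3/5.8)² = 124.0
- Glucose: 2 × 7.849 × (1.7/0.6)² = 126.0

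With 125 per arm the standard error is SD × √(4/250).

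- Waist: SE 2.062 cm, 5.8/2.062 = 2.813, power 80.3%
- Glucose: SE 0.2150 mmol/L, 0.6/0.2150 = 2.790, power 79.7%

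The 80%-power differences are 2.8016 × 2.062 = 5.78 cm and 2.8016 × 0.2150 = 0.602 mmol/L. The stated figures are therefore those of an individually randomised trial of 250, with no margin to absorb clustering.

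**Step 2: apply the design effect for randomised teams.**

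Completers per team: m = 250/29 = 8.62

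DE = 1 + (m − 1) × ICC

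SE = SD × √(4 × DE/250)

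For example, at ICC 0.03: DE = 1 + 7.62 × 0.03 = 1.23; waist SE = 16.3 × √(4 × 1.229/250) = 2.285; 5.8/2.285 = 2.538; power = Φ(2.538 − 1.96) = 71.8%.

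| ICC (assumed) | DE | Waist power | Waist, t on 27 df | Glucose power | Glucose, t on 27 df | 80%-power difference, waist | 80%-power difference, glucose |
|---|---|---|---|---|---|---|---|
| 0.005 | 1.04 | 78.8% | 75.9% | 78.2% | 75.2% | 5.9 cm | 0.61 mmol/L |
| 0.01 | 1.08 | 77.4% | 74.4% | 76.7% | 73.7% | 6.0 cm | 0.62 mmol/L |
| 0.03 | 1.23 | 71.8% | 68.7% | 71.1% | 68.0% | 6.4 cm | 0.67 mmol/L |
| 0.05 | 1.38 | 66.8% | 63.6% | 66.1% | 62.9% | 6.8 cm | 0.71 mmol/L |

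The power columns without a t reference and the detectable differences use the normal approximation. The t columns use 29 − 2 = 27 df.

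**Step 3: sensitivity to the other assumptions.** With 20 teams instead of 29, m = 12.5; at ICC 0.05 the DE is 1.575 and waist power is 61.1%. With 29 teams of unequal size (assumed coefficient of variation 0.5), waist power at ICC 0.05 is 63.5%. Both use the normal approximation.

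**Step 4: the possible offset from baseline waist.** If baseline is used efficiently, the SD is multiplied by √(1 − r²), where r is the correlation between baseline and 12-month waist. Holding DE fixed, 80% waist power is regained at these values of r:

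- DE 1.20: about 0.40 (normal) or 0.47 (t on 27 df)
- DE 1.38: about 0.52 (normal) or 0.57 (t on 27 df)

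For a plain change score the SD is multiplied by √(2(1 − r)), and the values are about 0.58 or 0.61 at DE 1.20 and 0.64 or 0.66 at DE 1.38. With r below 0.5, a change score would lower power further.

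**The case against.** The best defence is that the power calculation uses the raw SD of 16.3 cm while the planned outcome is change from baseline in a mixed model. Waist may be well correlated with its own baseline. At r = 0.7 and ICC 0.05, efficient baseline adjustment would give about 92% power (90% with t on 27 df). A reader might infer from the table above that the trial cannot detect 5.8 cm with 80% power. The document does not support that: it gives neither an ICC nor a baseline correlation, so actual power could lie on either side of 80%. This limits what can be claimed. It does not rescue the stated figure, because the article neither makes this argument nor supplies the correlation it would need.

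Other points for the plan:

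- **The loss may be small.** At ICC 0.005 waist power is 78.8%, and at 0.01 it is 77.4% by the normal approximation, against a claim of approximately 80%. The t reference on 27 df costs about 3 points even without clustering (77.4% at DE 1), and it is an analytic choice the article does not state. This is fair, and it is why a range is shown.
- **The Committee's 20% belonged to another design.** A reader might take it as a design effect of 1.20 for the current trial, giving 72.8% for waist. It was advice for 64 nurses with 10 patients each, and the Committee later approved 275 without it. It is not evidence about the ICC between these teams. Equally, approval of the target does not make the power statement right.
- **The analysis accounts for teams.** The primary model clusters on team, so nothing here shows harm to the effect estimate or to type I error. The defect lies in the planning statement.
- **The dropout step is immaterial.** 275 × 0.9 = 247.5 completers rather than 250 gives 79.9% waist power without clustering, which is still approximately 80%.

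**Conclusion.** The point holds as an error in the stated power and its justification. The claim of approximately 80% for 5.8 cm and 0.6 mmol/L is the figure for design effect 1, in a trial that randomises and clusters on teams. The reason for dropping the allowance is incorrect.

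On the article's own inputs without baseline adjustment, waist power is about 77%, 72% and 67% at ICC 0.01, 0.03 and 0.05, and glucose power about 77%, 71% and 66%. Each is about 3 points lower with t on 27 df. The waist difference detectable with 80% power is about 6.0 to 6.8 cm over that ICC range (normal approximation). Any positive ICC moves power in the same direction; its size rests on the assumed ICC, all 29 teams joining, 1:1 allocation and equal team sizes. A baseline correlation of roughly 0.5 to 0.6, used efficiently, could bring waist power back to 80%. The conclusion is therefore that the stated figure is not derived for this design, not that the trial is shown to be underpowered.

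**What to change.** 1. In the Discussion section on changes in study design, delete the statement that clustering need not be accounted for, together with the per-nurse reasoning behind it.
2. In Participants, restate power or the detectable difference for 275 enrolled, for both waist and glucose, as a team-randomised design. Give the expected number of participating teams, expected completers per team, a between-team ICC range (for example 0.01 to 0.05) and the reference distribution used.
3. If the calculation relies on baseline waist, state the assumed correlation, its source, and whether the model adjusts for baseline or analyses a change score. Do the same for glucose if it is treated that way.

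The figures above are illustrations on assumed ICCs. The restated numbers should come from the ICC range and team counts the investigators can defend. The change is to wording only and needs no extra patients; its cost is a less favourable stated figure unless a baseline correlation is documented.

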## Abbreviations

BMI: Body mass index
FFQ: Food frequency questionnaire
RCT: Randomised controlled trial
SD: Standard deviation
SMI: Severe mentally ill
TLM: Traffic light method for somatic screening and lifestyle
